### Frequency

The main aim of this study is to essentially ‘control’ for the possible effect of frequency. It might not be feasible to manipulate the relative syntactic frequency of a structure in a language. However, at the lexical level, verb bias (or the frequency with which verbs appear in different structures) influences both production [35] and comprehension [36]. While most of the previous studies did not address this variable in their materials, one study by Jackson et al. [15] attempted this by using the progressive participle ‘-ing’ in English (which is less frequent than the simple active verb form and is somewhat comparable to the passive) in combination with the past tense instead of simple present active structures. This has two potential issues; the first is we interpret thematic role processing as the assignment of agent/patient role to the first/second noun phrase in the study, and the active voice has several verb forms such as the simple form in which the first noun phrase is the agent, and when considered as a collective as they should be, these occur more frequently than the passive form. The second issue is whether the additional progressive aspect information deviating from the canonical default of the simple present active compared to passive will elicit a different neural signal is unknown. In our study, we will attempt to control verb bias by incorporating verb pairs that fulfil either of the two criteria:

A verb with higher token frequency in its passive form compared to its active form.A verb with the same frequency class* for both the passive and the active form.

*Frequency class is a number assigned to a group of words whereby this number does not often change in different corpora. The calculation is as follows: The frequency of the most frequent word in the corpus is divided by the frequency of the specific word, and log base 2 of the result is rounded up to the closest whole number.

We used the *Indonesian mixed corpus*, which is the largest Indonesian online corpus in the Leipzig Corpora Collection [37]. The distribution and descriptive information of the frequency can be seen in Fig 1 and Table 3, respectively (for full frequency information about the verbs, see S2 Appendix in S1 File). In Fig 2, log-transformed frequency values of active verbs are deducted by log-transformed frequency values of passive verbs. The general pattern is not only are they relatively comparable, but if anything, the passive verbs are slightly more frequent for some pairs. Extremely rare words (with a frequency class of 20 or higher) will not be used in this study, as the highest frequency class is 17 and the lowest is 7.

**Fig 1 pone.0272207.g001:**
[figure not shown]
Beeswarm plot of log-transformed passive and active verb frequencies.

**Fig 2 pone.0272207.g002:**
[figure not shown]
Beeswarm plot of log-transformed difference between active and passive (active–passive).

**Table 3 pone.0272207.t003:** Descriptives of verb frequency information.

	Active	Passive
Mean	21513.1	26415.88
SD	30110.56	50517.23
*Range*	124326	342184
*Min*	301	411
*Max*	124627	342595

### Procedure

Participants will read the participant information sheet, fill out a questionnaire about their demographic details, and sign the informed consent form.

Participants will be seated in front of a presentation monitor on which the sentences will be presented using E-Prime software, and the experiment will start with written instructions that will be explained orally by the experimenter. During the whole experiment, a fixation cross will be shown between trials and sets. Prior to the experiment, participants will be instructed to minimize their head movements during the trials and not to close their eyes while performing the experiment, although they will not be asked to refrain from blinking.

After every 3–8 trials (randomized), participants will be given a comprehension prompt. For the experimental items and filler cleft sentences, the comprehension prompt will be a yes/no question to probe the thematic role assignment (e.g., Did the police shoot the robber?/Did the robber shoot the police?). For the filler questions, the comprehension prompt will be a sentence that appropriately responds to the question (e.g., the adventurer noticed an officer patrolling) or if the noun phrase in the question is presented as the theme (e.g., the officer called the adventurer), and participants will have to judge whether the sentence is an appropriate response to the question (e.g., they should respond "yes" if they see "the adventurer noticed an officer patrolling" after this filler). These prompts are designed to ensure that the participants remain focused and parse the trials displayed, as well as to provide a measure of comprehension performance.

To avoid fatigue, there will be pauses after every block consisting of 30 trials (10 blocks in total), where the participants can take a break and resume the experiment whenever they are ready. The total test session, including cap and electrode preparation, will take approximately one and a half hours per participant.

### EEG recording and preprocessing

EEGs will be recorded using 64 Ag-Acl electrodes that will be attached to the participant’s scalp via an elastic cap with a 10–20 system. Conductive gel will be used. The cap has two dedicated electrodes for the left and right mastoids. To monitor horizontal and vertical eye movements, two electrodes are fixed in the outer canthi of each eye, and one more will be placed below the left eye (the VEOG above the left eye is integrated in the cap). Electrode impedances will be kept below 5k Ω. The EEG will be amplified and digitized with a sampling rate of 1000 Hz with an analog bandpass filter of 0.03-100Hz. The amplifier that will be used is the SynAmps 2 (NeuroScan, Charlotte, NC, United States), and the cap will be the 64-channel Quik-Cap Neo Net (NeuroScan, Charlotte, NC, United States). Stimtracker (Cedrus) will provide an interface between the experiment presentation software and EEG acquisition. Continuous EEG data will be acquired using Curry 7 acquisition software (Compumedics NeuroScan) whereby the files will be exported to the.cnt format and analysed using EEGLAB [38] for the preprocessing, and FieldTrip [39] for the statistical analysis.

The EEG data will be re-referenced to the two mastoid electrodes. The ERPs will be calculated per participant, per electrode, and per condition in intervals of 200ms before onset to 1000ms after onset for each time-locked trigger. These epochs will then be demeaned per channel in each epoch (the mean of the data from the entire epoch will be subtracted from each data point, as this may result in better ICA decompositions than baseline-correcting based on pre-stimulus interval; [40]. The epochs will then be subjected to an independent component analysis using the runica() command in EEGLAB [41]; this will divide the data into many independent components corresponding to the number of channels, excluding mastoid electrodes, EOGs, and bad channels that are previously marked. These components will be inspected visually to identify blinks and saccades, and components that are identified as blinks or saccades will be removed (a maximum of four components per participant can be removed, and if the number of components removed exceeds this, the participant will be excluded from the analysis). After the removal of components corresponding to blinks and saccades, baseline correction will be applied to the data with a 200 ms pre-stimulus onset baseline. Next, the epochs will be run through a moving window peak-to-peak threshold function for artefact detection; epochs with artifacts will be marked for removal based on this criterion. Lastly, the data will be filtered using a 0.1–40.0 Hz bandpass filter via the pop_eegfiltnew() default EEGLAB function.

There is an alternative method of *not* using baseline corrections, as suggested by Wolff et al. [16] and Friederici, Wang, Herrmann, Maess, & Oertel [42] who conducted sentence processing experiments. The reasoning behind this approach is that in the mid-sentence time windows, the waves of each trial may not be identical prior to the onset of the critical word, therefore potentially distorting the baseline. Wolff et al. [16] instead used narrower bandpass filters (0.3–20.0Hz) to exclude slow drifts while still including language-related ERPs. However, Steinhauer [43] criticized the use of a higher filter instead of baseline-correction because first of all, the modified filter does not distinguish between artifacts (slow drifts) and real slow waves related to language processing; moreover, the filter converts sustained effects into apparent local effects such as ELANs, and finally, the increased filtering does not directly address the problem of a distorted baseline resulting from differences before the onset of the critical region. We therefore will adopt a 200ms baseline in this study.

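### The 0.1–40 Hz filter is the last step, after baseline correction of 1.2 s epochs, so the pre-stimulus mean is no longer zero when the data are tested

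*Protocol article*

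**What the plan says.** All of this is in the Protocol article, section EEG recording and preprocessing, unless another section is named.

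- Recording uses "a sampling rate of 1000 Hz with an analog bandpass filter of 0.03-100Hz". This is the only filter stated before epoching.
- ERPs are computed "in intervals of 200ms before onset to 1000ms after onset for each time-locked trigger", which gives 1,200 samples per epoch.
- Epochs are demeaned, decomposed by ICA and cleared of blink and saccade components. Then "baseline correction will be applied to the data with a 200 ms pre-stimulus onset baseline".
- Artefact marking comes after that, still on data without an offline filter: "Next, the epochs will be run through a moving window peak-to-peak threshold function for artefact detection".
- The closing step reads: "Lastly, the data will be filtered using a 0.1–40.0 Hz bandpass filter". EEGLAB's default filter routine is named for it, and the description of preprocessing steps ends there.
- The next paragraph discusses dropping the baseline in favour of a 0.3–20 Hz filter. It reports the criticism that "the filter converts sustained effects into apparent local effects", and concludes: "We therefore will adopt a 200ms baseline in this study".

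The Statistical analysis plan section tests every scalp electrode over the full interval after onset, with a cluster threshold of p < .1 chosen for sensitivity to faint, prolonged differences. The Predictions section expects a positivity for the passive at 500–700 ms on the verb and a negativity at 300–600 ms on NP2.

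**The concern.** Baseline correction sets the mean of the 200 ms before onset to zero in every epoch and channel. A high-pass filter applied afterwards subtracts a slow moving average, and nothing keeps the pre-stimulus mean at zero. The 200 ms baseline that the protocol deliberately adopted is then not in force when active and passive are compared.

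The epoch is also very short for a 0.1 Hz cutoff. Most of what the filter averages over is padding beyond the epoch, so a choice the protocol does not state shapes the result.

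Three things are at stake for a difference that persists to the end of the epoch: its size in the later window, a false shift of opposite polarity before it begins, and its apparent latency. The early interval is inside the tested range, and prolonged effects are what the cluster threshold is meant to catch. A shrunken effect also favours a null result, which the Predictions section would read as a sign that earlier findings were confounded by syntactic frequency.

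**Working it through.** The protocol gives no figure of its own to reproduce here, so the check simulates the stated order.

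**Inputs from the protocol.** Epoch −200 to 1000 ms, 1000 Hz sampling, lower cutoff 0.1 Hz, baseline −200 to 0 ms, predicted windows 500–700 ms and 300–600 ms.

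**Assumptions.** Zero-phase Hamming-window FIR with a 0.1 Hz transition width. Three ways of extending the epoch: edge value held constant, mirrored, or zeros.

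**Scale.**
- One 0.1 Hz cycle lasts 10 s, and 1.2 / 10 = 0.12 of a cycle.
- Kernel length is 3.3 / (0.1 / 1000) = 33,000 samples (33,001 taps), and 33,000 / 1,200 = 27.5 epochs.
- Half-amplitude cutoff is 0.1 − 0.1/2 = 0.05 Hz.

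**Unit difference from 500 ms to epoch end, filtered last as written** (truth: 0 / 0 / 1):

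| Padding | Baseline | 0–300 ms | 500–700 ms |
|---|---|---|---|
| Edge constant | −0.44 | −0.46 | 0.49 |
| Mirror | −0.41 | −0.41 | 0.59 |
| Zero | −0.05 | −0.05 | 0.95 |

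**Hand check.** The average that is subtracted has a weight near its centre of about 2 × 0.05 = 0.1 per second.
- Zero padding: 0.1 × 0.5 s = 0.05 is subtracted everywhere.
- Edge constant: the average is 0.5 at the step and changes by 0.1 per second away from it. At the middle of the baseline (0.6 s before the step) it is 0.5 − 0.06 = 0.44. At 150 ms it is 0.5 − 0.035 = 0.465. At 600 ms it is 0.5 + 0.01 = 0.51, which leaves 0.49.
- Mirror: the average is roughly the epoch mean, 500 / 1,200 = 0.42, which agrees with the simulated 0.41 to within about 0.01.

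**Effects confined to the predicted windows** (share kept in the window; the rest appears as an opposite-sign offset elsewhere):
- 500–700 ms: 0.98 with constant or zero padding (0.1 × 0.2 s = 0.02 lost); 0.83 with mirroring (200 / 1,200 = 0.17 lost).
- 300–600 ms: 0.97 with constant or zero padding (0.1 × 0.3 s = 0.03 lost); 0.75 with mirroring (300 / 1,200 = 0.25 lost).
- For comparison, 500–900 ms keeps 0.96, or 0.67 with mirroring.

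**Other filters.** With zero-phase Butterworth band-passes and an effect lasting to epoch end, the baseline was −0.12 to −0.58 and 0–300 ms was −0.28 to −0.62. The sign was reversed in every variant. For effects that returned to zero before 1000 ms, a few Butterworth paddings gave a small shift of the same sign.

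**Noise.** With assumed 1/f noise of SD 10, the single-trial baseline mean is exactly 0 before the filter. Afterwards its SD is 0.6 (zero padding), 4.8 (mirror) or 6.3 (constant).

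**Baseline correction repeated after the filter** (subtracting the new baseline from the table values):
- Edge constant: 0–300 ms −0.46 + 0.44 = −0.02; 500–700 ms 0.49 + 0.44 = 0.93.
- Mirror: 0.00; 0.59 + 0.41 = 1.00.
- Zero: 0.00; 0.95 + 0.05 = 1.00.

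**Continuous data filtered first, then epoched and baseline-corrected.** For an effect with a gradual onset whose true 500–700 ms mean is 0.94, lasting to 1–3 s, the baseline is 0, 0–300 ms lies between −0.005 and −0.001, and 500–700 ms lies between 0.92 and 0.94.

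**The case against.** The best defence is that the damage may be small. Kernel length and edge handling are assumptions, and with zero padding the leak is about 5% even for the least favourable waveform. The Predictions section names bounded windows, for which the loss is 2–3% unless the edges are mirrored. This stands, and it limits what can be claimed.

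Four stronger readings are tempting, and the document does not support them:

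- **The predicted effects are halved.** The value of 0.49 needs an effect that never returns to zero within the epoch, together with edges held constant. For effects confined to the predicted windows the largest loss found is 25%.
- **The test result is an artefact.** Both conditions pass through the same filter and labels are permuted within subject. Nothing here shows a raised familywise error rate. What is exposed is the size, polarity and timing of a real sustained effect, and the power to detect it.
- **Unfiltered ICA and artefact detection will push participants below the 25-trial minimum.** The peak-to-peak threshold is not given, the detector uses a moving window, and the epochs are already baseline-corrected. Loss of trials cannot be derived.
- **The protocol does exactly what it criticises.** The criticised filter was 0.3–20 Hz and used in place of a baseline. The protocol's cutoff is milder and is combined with one. The fault is the order, which undoes the chosen baseline.

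None of this rescues the sequence. The text does not secure the benign padding, and even that case leaves a non-zero baseline.

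**Conclusion.** The point holds as a fault of processing order. The protocol filters last and does not re-baseline, so the adopted 200 ms baseline is not in force at testing and the output depends on unstated edge handling.

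For a difference lasting from 500 ms to epoch end, the assumed FIR filter moves between 0.05 and 0.46 of it, with reversed sign, into the baseline and 0–300 ms, and leaves 0.95 to 0.49 at 500–700 ms. The reversed sign is firm for effects of that kind, since it appeared under every filter and padding tried. The size is not firm, because it rests on the assumed kernel and padding. For effects confined to the predicted windows the loss is 2–3%, or 17–25% with mirrored edges.

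The order should be corrected before the data are analysed. In a registered report, choosing it afterwards would be a post hoc deviation.

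**What to change.** Preferred order: filter the continuous recording at 0.1–40 Hz; epoch; demean for ICA as already planned; remove components; apply the 200 ms baseline correction; run artefact detection on those epochs.

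Minimum change: keep the present order, but apply or repeat the 200 ms baseline correction after the final filter, and state the filter's transition width and edge handling.

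The cost is a small edit to the preprocessing script and to one paragraph of the protocol. No new data are needed.

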### Materials

Participants will read stimuli comprising 100 semantically reversible active and passive sentences (see S1 Appendix in S1 File). Examples of which are shown in Table 2.

**Table 2 pone.0272207.t002:** Stimuli examples of each condition.

Condition	NP1	Art	VP	Adjunct	NP2	PP/RC
Active	Polisi	itu	menembak	langsung	seorang perampok	di malam hari.
	Police	that/the	**ACT**shoot	immediately	(a) robber	at night.
		(the/a) police immediately shoots (the/a) robber at night.				
Passive	Polisi	itu	ditembak	langsung	oleh perampok	di malam hari.
	Police	that/the	**PAS**shoot	immediately	by robber	at night
		(the/a) police is immediately shot by (the/a) robber at night				

The sentences involve an animate subject and object and are constructed while avoiding a plausibility bias. Word order is manipulated by using two structures: simple active and simple passive sentences. Based on previous studies on processing well-formed sentences, the contrast of interest is passive-active, and whether the effects of the word order persist. We will strive for active-passive pairing plausibility with the use of NP1 and NP2 that are plausibly reversible (i.e. each sentence should not be strongly biased to one interpretation due to the nouns used). Additionally, there will be 200 filler trials consisting of questions (e.g. What did the adventurer notice yesterday?) and cleft sentences (e.g. it is the boy who the girl is calling) to prevent the habituation of the participants. The task for both the experimental and filler sentences will be discussed in the Procedure. The stimuli will be tested for acceptability and prototypicality using an online survey method utilizing a Likert scale of 1 to 7 with a similar setup used by Jackson, Lorimor, & van Hell [15]. Assuming the materials are rated acceptable and plausible by raters, the materials will not be further edited.

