The materials will be presented visually and word-by-word for 500ms with a 100ms blank screen between each word. Each trial begins with a blank screen of 750ms followed by the word ‘*siap*?’ (ready?), which stays on the screen until participants presses any keys. There will be two lists of sentences each pseudorandomized into 10 sets (each set containing 10 experimental sentences and 20 fillers). Digital triggers will be manually inserted at three time points in every sentence: at the onset of the verb (i.e., the onset of the prefix), and at the onset of NP2. Additionally, NP1 data points will be extracted from -1400 to -200 before the verb onset to be used as a sanity check to see if there are baseline differences between the conditions. It is important to note that the triggers will be located in the middle of the sentence.

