In general, for the time windows and specific components, due to the nature of cluster-based permutation where adjacent sites and time points are correlated, we will be looking at the whole epoch (here we theorize that a ‘real’ effect should persist through multiple adjacent electrodes and a chunk of tens to hundreds of milliseconds/samples–a more detailed description of the procedure is provided by [45]). However, were there to be an effect in either the verb or NP2 (as per the predictions above), we expect it to be observed in the time windows and distributions corresponding to the LAN, N400, and/or P600 –all of which have been observed in similar studies and above 300ms. Specifically, for the verb, we would expect the passive to be more positive than the active for the 500-700ms time window, as this was what the study closest [15] to this one reported in their critical region. For NP2, we expect some form of negativity to occur for the passive compared to the active between the 300-600ms time window–this was observed in studies which reported ERPs post-disambiguation.

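### The local NP2 baseline falls 1000–1200 ms after the verb, an interval no planned check covers, so a fading verb positivity could pass for the predicted NP2 negativity

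*Protocol article*

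**What the plan says.** All of this is in the protocol article.

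- **Presentation (Materials).** "The materials will be presented visually and word-by-word for 500ms with a 100ms blank screen between each word". Table 2 shows the order NP1, article, verb, one-word adjunct, NP2.
- **Triggers (Materials).** They are placed "at the onset of the verb (i.e., the onset of the prefix), and at the onset of NP2".
- **Epochs and baseline (EEG recording and preprocessing).** ERPs are computed in "intervals of 200ms before onset to 1000ms after onset for each time-locked trigger", and each epoch is corrected on the 200 ms before its own onset. No separate rule is given for NP2. The section acknowledges that mid-sentence waveforms may already differ before the critical word and so distort a baseline. It rejects stronger filtering, in part because filtering leaves that problem unsolved, and concludes: "We therefore will adopt a 200ms baseline in this study".
- **Baseline check (Materials).** "NP1 data points will be extracted from -1400 to -200 before the verb onset", as a sanity check on differences between the conditions.
- **Predictions.** At the verb, the passive should be more positive than the active at 500–700 ms. "For NP2, we expect some form of negativity to occur for the passive compared to the active", at 300–600 ms.
- **Purpose of NP2.** The section on the present study examines NP2 for spill-over from the verb. Materials asks whether the word-order effect persists.

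**The concern.** A pre-stimulus baseline is safe when the two conditions do not differ in it. That is plausible before the verb, because the Table 2 sentences are identical up to that point. It is not assured before NP2, because the verb prefix has already told the reader which structure this is, and the protocol itself predicts a response to it.

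Two readings could then go wrong. A verb positivity that lingers into the NP2 baseline and fades afterwards would appear as a passive negativity at NP2. Predictions explains the verb effect by thematic revision and the NP2 effect by a generalised processing cost, so one verb effect could be taken as support for two mechanisms. Conversely, a positivity that carries on unchanged would be subtracted out of the NP2 epoch and look like no spill-over. In both cases the persistence question cannot be answered from the locally baselined NP2 epoch alone.

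**Working it through.** **1. Timing, checked against the protocol's own figure.** Word interval = 500 + 100 = 600 ms. Table 2 has two words (NP1, article) before the verb, so NP1 onset = -2 × 600 = -1200 ms. Its epoch is -1200 - 200 = -1400 ms to -1200 + 1000 = -200 ms. This reproduces the stated extraction window exactly and confirms the layout.

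**2. Location of the NP2 baseline.** With one adjunct word, and the trigger on the first word of NP2:

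- NP2 onset = 2 × 600 = 1200 ms after the verb
- NP2 baseline = 1000 to 1200 ms after the verb
- predicted NP2 window = 1200 + 300 to 1200 + 600 = 1500 to 1800 ms after the verb

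**3. What covers that interval.** The NP1 check spans -1400 to -200 ms and the verb test 0 to 1000 ms. Overlap with 1000–1200 ms is zero in both cases. The cluster test takes data that are already baselined and looks only at the post-stimulus part of each epoch. The check also stops short of the verb's own baseline (-200 to 0 ms).

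**4. Size.** The document gives no amplitude, so this is an assumption: a passive-minus-active difference of 1 microvolt up to time *s*, then exponential decay with time constant τ, and no true NP2 effect. The mean over a window from *a* to *b* is

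τ/(b - a) × [exp(-(a - s)/τ) - exp(-(b - s)/τ)]

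Example, *s* = 700, τ = 300:

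- baseline: 300/200 × [exp(-1) - exp(-1.667)] = 1.5 × (0.368 - 0.189) = 0.27
- NP2 window: 300/300 × [exp(-2.667) - exp(-3.667)] = 0.069 - 0.026 = 0.04

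Apparent NP2 effect = residual in the NP2 window minus baseline mean (differences taken before rounding):

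| Verb effect | Mean in 1000–1200 ms | True residual in 1500–1800 ms | Apparent NP2 effect |
|---|---|---|---|
| Over by 1000 ms | 0 | 0 | 0 |
| Decay from 700 ms, τ = 300 | 0.27 | +0.04 | -0.22 |
| Decay from 700 ms, τ = 600 | 0.52 | +0.21 | -0.31 |
| Decay from 1000 ms, τ = 300 | 0.73 | +0.12 | -0.61 |
| Decay from 1000 ms, τ = 600 | 0.85 | +0.34 | -0.51 |
| No decay | 1.00 | +1.00 | 0 |

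**5. A second waveform.** Take a 2 microvolt effect on a plateau to 700 ms, then linear decay to zero, again with no NP2 effect. The apparent NP2 effect is 0 if the decay ends at 1000 ms, -0.40 at 1200 ms, -0.86 at 1400 ms and -1.07 at 1600 ms. As shares of the verb effect, -0.40/2 is 20% and -1.07/2 is 54%. On a pre-verb baseline the same four cases give 0, 0, 0 and +0.04.

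**The case against.** The strongest reply is that the predicted verb effect may be over in time. Its window ends at 700 ms, and the Basque verb positivity in Table 1 ends at 900 ms. No positivity at the verb in the cited work is reported past 900 ms. The one cited verb effect that may reach beyond 1000 ms is the Japanese one (650–1050 ms in the text, 650–1000 ms in Table 1). It is a negativity, which would push NP2 in the opposite direction. This stands: the artefact is a risk and not a forecast, and its sign depends on the sign of what lingers.

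A reader might infer that the false NP2 effect would be nearly as large as the verb effect. The figures do not support that; none of the cases above exceeds about 60% of it.

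A reader might also infer that the study's main conclusion is compromised. It is not. The verb is the main region, and its baseline precedes the divergence. The frequency interpretation in Predictions requires no effect at both verb and NP2. The artefact needs a real difference after the verb, so it cannot falsely overturn that joint null. Where a steady effect is removed from NP2, it remains visible in the verb epoch.

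The protocol did consider the baseline problem and gave reasons for its choice. That argument compares a local baseline with no baseline plus a narrower filter. It does not consider a common pre-verb baseline, and its choice leaves NP2 exposed to the problem it names.

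Finally, the timing comes from one example. Adjunct lengths across items are not shown, nor is the exact NP2 trigger word. If the trigger sits on the noun, the baseline moves to 1600–1800 ms. That is further from the verb but still unchecked, and it follows words that differ by condition.

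**Conclusion.** The point holds as a conditional weakness of the NP2 analysis. For the Table 2 layout, the NP2 baseline lies 1000–1200 ms after the verb, the conditions have already diverged, and no planned analysis examines that interval. A passive positivity that reaches it and then fades would yield a spurious NP2 effect of the predicted sign. For an assumed 1 microvolt verb effect, this runs from 0 through about -0.2 to -0.3 up to about -0.5 to -0.6, where the true residuals are 0 to +0.34. A steady positivity would be hidden, and a lingering negativity would reverse the sign.

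At stake is the reading of NP2 as spill-over or as a separate effect. The verb contrast and the joint-null conclusion are largely unaffected. Should-fix. Confidence is medium, because the full item timing and trigger placement are not shown and the amplitudes are assumed.

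**What to change.** Keep the local-baseline NP2 analysis and prespecify three additions:

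1. **A companion NP2 analysis.** Cut one long verb-locked epoch, baselined on the 200 ms before the verb. For the Table 2 timing it must run from -200 ms to 1200 + 1000 = 2200 ms. If the trigger is on the noun, it must run to 1800 + 1000 = 2800 ms.
2. **A wider baseline check.** Add the 200 ms before NP2, measured against the pre-verb baseline, because the local baseline sets its mean to zero by construction. Add -200 to 0 ms before the verb for completeness, measured for the same reason against an earlier baseline.
3. **A reading rule.** An NP2 effect counts as separate from the verb effect only if it appears under both baselines, or if the pre-NP2 interval shows no condition difference. In every decaying case tabulated above, the pre-verb baseline gives a small positive value and the local baseline a negative one, so the spurious negativity would fail the first condition.

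The protocol should also state the adjunct length across items and the word that carries the NP2 trigger.

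The cost is a script change and a short paragraph. Longer epochs lose some further trials to artefacts, which matters for the minimum of 25 trials per condition. They also place the NP2 window 1.5–1.8 s after its baseline, where drift is larger and verb carry-over stays in the signal. For that reason the long epoch should accompany the planned analysis and not replace it, and trial exclusions should be reported separately for each.
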